#### **9.10 Methods secondary analysis**

For analysis of secondary outcomes the same methods will be used as for the primary hypothesis.

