## 2 Introduction

### Low protein in infant nutrition

An adequate supply of dietary protein is essential for healthy growth and development in infancy. Protein is the major functional and structural component of all cells, and amino acids play an important role as precursors of coenzymes, hormones, nucleic acids and other essential molecules.

Human milk is recognized as the optimal source of nutrients for infants throughout at least the first year of life. The dietary reference intakes (DRI) for infants up to the age of 6 months are based upon data of breastfed infants receiving human milk as the principal source of nutrients. The protein DRI recommendation for infants is 1.52 g/kg/d, which is based upon an estimated average milk intake volume of 0.78 L/d and a mean protein content of human milk of 11.7 g/L during the first six month of life.

As amino acid composition of cow's milk protein, used in manufacturing infant formula, does not perfectly match the amino acid composition of human milk, infant formula contains more protein than breast milk. This is to guarantee that all amino acids supplied meet quantitatively the amounts of amino acid present in human milk.

The protein content reduction of the intervention formula has been made possible by the development of a protein mix based on cow's milk protein sources enabling to achieve an amino acid profile closer to that of human milk, in particular lowering threonine and increasing tryptophan levels. The highly nutritious native whey protein isolate has a high content of  $\alpha$ -lactalbumin obtained by careful fractionation.

Recent evidence suggests that higher protein intakes during infancy might be associated with an increased risk of excessive weight gain. A higher habitual protein intake between the age of 12 and 24 months was associated with a higher body mass index (BMI) in girls, but not boys. Furthermore, consistent high protein intake during the first year of life was associated with a larger BMI and increase in % body fat at the age of 7. Breastfeeding has been associated with a modest, but protective effect against childhood obesity. Speculations point towards the lower protein content of human milk as one possible protective reason.

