The lowest acceptable protein/energy ratio for cow's milk-based infant formula, as defined by the EU Directive 2006/141/EG, is 1.8 g/100kcal (see below); the same value has been recommended by the European Society for Paediatric Gastroenterology, Hepatology and Nutrition, the Codex Alimentarius and the Committee on Nutrition of the American Academy of Pediatrics. However, according to the EU Directive, the suitability of an infant formula containing less than 2 g of protein per 100 kcal has to be shown in an appropriate research study.

Dietary intake of long-chain polyunsaturated fatty acids (LCP) such as arachidonic acid (ARA, C20:4n-6) and docosahexaenoic acid (DHA, C22:6n-3) has been shown to be important for optimal infantile development. If LCP intake through breastfeeding is not possible, because the infant is no longer breastfed, the use of an LCP-enriched formula is recommended by experts. The addition of LCPs enables formula-fed infants to reach an LCP status comparable with that of breastfed infants, which supports optimal visual and cognitive development. The modified, low-protein infant formula will contain 12.3 mg/100 kcal LCPs, corresponding to 0.23% each ARA and DHA of total fatty acids. It is a secondary goal of the study, to investigate whether infants receiving the low-protein LCP enriched infant formula show higher LCP plasma phospholipids concentrations compared to infants receiving the standard formula without LCP and, thus, are more similar to fully breastfed infants.

In order to provide non breastfeed infants with the best nutrition possible the BEMIM trial is designed to 1) assess the suitability of a modified, low-protein infant formula (1.89 g/100 kcal) compared with a standard formula for the particular nutritional use of healthy term infants during the first four months of life and 2) to show that parameters of protein status are closer to that of breastfed infants.

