### 3 Study Objectives

According to Article 7 of the European Directive on Infant and Follow-on Formula 2006/141/EC appropriate studies are required to show that an infant formula with a protein content of less than 2 g/100 kcal is suitable for the particular nutritional use of infants.

Against this background the primary objective of this study is to show non inferiority of an infant formula with a protein content of 1.89 g/100 kcal compared to a standard infant formula with a protein content of 2.2 g/100 kcal referring to growth parameters of healthy term infants receiving this formulas fully during the first 4 months of life after establishment of full formula feeding no later than postnatal day 28.

The secondary objective of the study is to show that parameters of protein status (serum albumine, blood urea nitrogen, serum creatinine, plasma amino acid-profile) in blood of infants receiving the modified infant formula (protein: 1.89 g/100 kcal) instead of the standard formula (protein: 2.2 g/100 kcal) are closer to that of fully breastfed infants. Furthermore fatty acid-profile will be assessed and compared between the groups.

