#### **8.5.1.5 Blood withdrawal**

In the context of blood sampling following aspects will be reported:

- Child fasted (last feeding at least 2 hours ago)
- Time of last feeding (hours)

- Amount of last feeding: complete meal / minor amounts
- Blood samples taken
- Enough blood taken
- Blood analyses results

Blood count analysis result must be filled in the CRF after completed analysis. Original reports must be attached after last page of the CRF.

Results from Munich (amino acid profiling, fatty acid profiling) will be reported in one table for all subjects. This list will be attached to the file where CRF are stored after completion of analyses.

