#### 8.8.2.1 Time of sample collection

As far as possible, fasted blood samples should be collected - that means at Baseline Visit soonest 2 hours after the last feeding, at Visit 4 soonest 3 hours after the last feeding. Time (hours ago) of last feeding as well as amount of the last meal (complete meal or minor amount) must be reported.

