### **9.9 Statistical analysis**

For all quantitative parameters determined a test for normal distribution will be performed according to Kolmogorov-Smirnov. If normal distribution can be assumed, mean and standard deviation will be given for these parameters. For non-normally distributed data median and interquartile range will be provided and data will be transformed appropriately prior to statistical analysis.

For the primary analysis breastfed children will not be included. They serve rather as a reference for the interpretation of the data collected in the formula groups.

The influence of the study group on the primary outcome will be tested using linear regression with baseline values as co-variables. Parameters, which might influence anthropometric development of the infant, e.g. gender, parental smoking and socio-economic status, will be tested for their effect on the outcome variable and, if appropriate, will be included as confounding factors.

Interim analyses are not foreseen as valuable results can not be expected from analysing the data from a limited number of subjects and an association of increased risk of occurrence of adverse events with any of the studied formulas is not conceivable.

Statistical analyses will be performed on the data collected from all infants enrolled into the study and randomised to one of the formulas (intention to treat analysis) and on the data collected from all subjects, who completed the study according to the protocol (per-protocol analysis). The per-protocol analysis is considered the primary analysis; the intention-to-treat analysis has confirmative character.

Full analysis (Intention-to-Treat = ITT Principal) comprises all subjects who were enrolled including those with minor and severe non-compliance to protocol, subjects with missing values (but who participated at least in Visit 1) and protocol violations. Solely subjects turned out to be a "screening failure" (does not fit to an important inclusion or exclusion criteria) will not be considered for full analysis.

The Per-Protocol Population (PPP) is defined as the set of subjects without severe non-compliance to the protocol. Minor non-compliance e.g. visit outside the given window, or missing values of marginal importance (stool colour not reported once) are acceptable and do not lead to exclusion from the PPP analysis.

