#### **9.11 Complementary analysis**

To confirm compliance with the study protocol energy intake and macronutrient intake as calculated from 3-day food protocols ("Diaries") will be compared by t-test between both intervention groups.

Plasma urea, amino acid levels and fatty acid composition will be considered as the main blood parameters measured in children and will be compared between both intervention groups.

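### The secondary objective claims protein markers closer to breastfed infants, but sections 9.10 and 9.11 specify only a formula-versus-formula comparison and no criterion for closeness

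*Protocol*

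**What the plan says.** **Objective.** Protocol section 3 and the synopsis aim to show that albumin, urea nitrogen, creatinine and the amino acid profile in infants on the modified formula "instead of the standard formula (protein: 2.2 g/100 kcal) are closer to that of fully breastfed infants". The introduction ends with the same aim: "to show that parameters of protein status are closer to that of breastfed infants". Section 7.2.2 lists these markers as secondary outcomes. The claim involves three groups.

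**Analysis.** Section 9.10 reads: "For analysis of secondary outcomes the same methods will be used as for the primary hypothesis". The primary method in section 9.9 is a linear regression of the outcome on study group, and there "For the primary analysis breastfed children will not be included". The next sentence of 9.9 gives those children the role of a reference for interpreting the formula data. Section 9.11 says that urea, amino acids and fatty acids "will be considered as the main blood parameters measured in children and will be compared between both intervention groups".

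Section 9.4 names only length gain and head circumference gain as secondary variables. Within section 9, the blood markers could therefore fall under 9.10 (through 7.2.2) or under 9.11, which does not mention albumin or creatinine. Neither section states a contrast with the breastfed group, a distance measure or a rule for *closer*.

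**The concern.** The planned contrast is intervention minus control, and the breastfed mean does not enter it. Whether a given formula difference brings a marker nearer to breastfed infants depends on where that mean lies. A lower value is closer if both formulas lie above it. It is further away if both lie below it, or if the modified formula overshoots far enough.

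The step from a formula difference to closeness is easy to take. The introduction does so for long-chain fatty acids, where higher levels than in controls are taken to mean greater similarity to breastfed infants. Single amino acids are deliberately moved in opposite directions ("in particular lowering threonine and increasing tryptophan levels"), and the ingredient list in section 6.1.1 includes added phenylalanine and tryptophan. The direction that counts as closer therefore need not be the same for every marker.

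At stake is the support for a claim that the protocol sets out to show. Section 13.3.2 foresees submission of results to EFSA.

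**Working it through.** **1. The plan's own figure.** Section 9.5 gives SD 6 g/day, a difference of 0.5 SD, one-sided 2.5% and 85% power. Section 9.2 gives the 3 g/day margin. Then n = 2 × [6 × (1.960 + 1.036) / 3]² = 71.8, so 72 per group against the stated figure of about 70. Power at 70 is 84.1% (normal approximation), and 70 / 0.70 = 100 recruited. The sample size reproduces and is not in dispute. No figure is given for the secondary objective.

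**2. What closeness requires.** Let C, S and B be the means for control, study formula and breastfed. Then

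(C − B)² − (S − B)² = 2 × (C − S) × [(C + S)/2 − B].

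The study formula is closer exactly when C − S and (C + S)/2 − B have the same sign. The plan tests only the first term.

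**3. Standard errors in SD units, 70 per group.**
- C − S: √(2/70) = 0.169
- (C + S)/2 − B: √(1.5/70) = 0.146
- With equal group sizes and variances the two contrasts are uncorrelated, so under normality their probabilities multiply.

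**4. Same formula difference, different positions of the breastfed mean.** The means are assumptions, expressed as SD from breastfed. In every row C − S = 0.5, so z = 0.5/0.169 = 2.96 and the power of the formula contrast is Φ(2.96 − 1.96) = 0.84. The closeness criterion requires both contrasts to be significant at one-sided 2.5% with the same sign.

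| Control | Study | Truth | Formula contrast significant | Closeness criterion met |
|---|---|---|---|---|
| +1.0 | +0.5 | closer | 84% | 84% |
| +0.25 | −0.25 | equally far | 84% | 2% |
| 0 | −0.5 | further away | 84% | 0% |
| −0.5 | −1.0 | further away | 84% | 0% |

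Row 1: the second contrast has z = 0.75/0.146 = 5.12, so its power is close to 1 and the product is 0.84. Row 2: the second contrast is null, so 0.84 × 0.025 = 0.02. A simulation with 200,000 runs gives the same values.

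**5. The price of the criterion.** Take control at +0.5 and the study formula exactly at the breastfed mean. The second contrast has z = 0.25/0.146 = 1.71, with power Φ(1.71 − 1.96) = 0.40. The product is 0.84 × 0.40 = 0.34, against 0.84 for the formula contrast alone. A bootstrap interval for the difference in absolute distances does about the same here (32%).

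**The case against.** The strongest reply is that the breastfed group is not discarded. Section 9.9 keeps it as a reference for interpretation, and section 9.1 promises a detailed description of all recorded data. A table showing all three means would make an overshoot visible. For urea and amino acids, section 2 reports that formula-fed infants run higher than breastfed infants. If both formulas lie clearly above the reference, a lower value is closer, and the formula contrast read beside the table is informative. The sentence in 9.9 excluding breastfed infants is also written for the primary analysis and reaches secondary outcomes only through 9.10.

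Much of this stands. A reader might infer that the plan cannot answer its question at all, or that the breastfed infants serve no analytic purpose. The documents do not support either: a descriptive reading is available, and the group also serves as the reference for growth, fatty acid status and tolerance. A reader might also infer that the formula contrast is likely to mislead. Nothing shows that. Section 2 presents the amino acid changes as bringing the profile nearer to human milk.

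A reader might further see a conflict in the fasting rules, because the blood-withdrawal record uses 2 hours while section 8.8.2.1 asks for sampling "at Visit 4 soonest 3 hours after the last feeding". That record (8.5.1.5) belongs to the Baseline Visit, and 8.8.2.1 sets 2 hours for Baseline, so the two agree.

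What the objection does not remove is the mismatch. A description ignores the uncertainty of the breastfed mean and has no fixed rule, while the objective is to *show* closeness. Nor is this only detail left to an analysis plan: section 9.11 states the two-group comparison outright for urea, amino acids and fatty acids.

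**Conclusion.** The point holds in a limited form. The stated analysis does not match the stated secondary objective, because the specified contrast omits the breastfed mean and closeness is left to informal reading. At 70 per group and a 0.5 SD formula difference, the planned contrast reaches significance in about 84% of trials in all four layouts examined. A criterion using the breastfed mean separates them (about 84% when closer, 2% when equally far, 0% when further away).

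These figures rest on assumed means, equal SDs, normality and 70 evaluable infants in each of the three groups. They show what the contrast can and cannot distinguish, not what the marker values are. The primary non-inferiority analysis is unaffected.

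**What to change.** In sections 9.10 and 9.11, add for each protein marker at Visit 4 a model with all three groups. Claim *closer* only if both of these are significant (one-sided 2.5% each) with the same sign:

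- control minus intervention
- the mean of the two formula groups minus breastfed

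An alternative aimed at the same claim is the difference in distance to the breastfed mean, with a confidence interval that includes the uncertainty of that mean. Name albumin and creatinine alongside urea and amino acids. Keep the randomised two-formula contrast beside it, and state that the breastfed comparison is not randomised, since section 4.2 leaves feeding mode to the parents. The model need not include baseline blood values: Amendment No. 2 dropped that sample and does not regard the adjustment as mandatory.

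**Cost.** Two short sections are rewritten and no new data are needed, because Visit 4 blood is already planned in all groups. The loss of power is real when the intervention mean is near the breastfed mean: about 32–34% against 84% with control 0.5 SD away. A failure to meet the criterion should therefore not be read as evidence against closeness. Amendment No. 3 reports that weight gain has already been analysed, so a criterion added after that should be labelled as such.

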#### **9.11 Complementary analysis**

To confirm compliance with the study protocol energy intake and macronutrient intake as calculated from 3-day food protocols ("Diaries") will be compared by t-test between both intervention groups.

Plasma urea, amino acid levels and fatty acid composition will be considered as the main blood parameters measured in children and will be compared between both intervention groups.

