### 7.3.2 Formula intake

In the context of the Visits, the reminder calls and the diaries filled out at home, formula intake will be reported by assessing:

- Visits/Reminder calls: formula meals per day, breastfeeding meals per day, meals of others
- Diaries:
  - number of bottles per day
  - intake of formula in ml per meal (documentation of prepared formula in ml and leftover in the bottle in ml)
  - acceptance of formula (good / reluctant / bad)

In the breastfeeding reference group similar dairies will have to be filled in asking also for feeding history (number of breast meals per day).

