### 9.2 Hypothesis to be tested

$H_0$  (to be rejected): The mean daily weight gain in the intervention group (formula with reduced protein content) is more than 3 grams per day lower than in the control group (standard formula).

$H_{\text{alternative}}$ : The mean daily weight gain in the intervention group (formula with reduced protein content) is not more than 3 grams per day lower than in the control group (standard formula).

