### 9.5 Sample size calculation

Based on previous publications and own data we can expect the children to grow on average 30 grams per day with a standard deviation of 6 grams between birth and 4 months of life. Growth studies should be designed to have a power to detect a difference in weight gain equal to 0.5 standard deviations according to the SCF report. Thus, one would need about 70 children in each formula group under the assumption of non-inferiority (one-sided test), a

significance level of 2.5% and a power of 85%. We expect a true loss-to follow-up of about 10-15%. Additionally, we expect that another 15% will switch formula due to preference changes which usually take place in the first months of life. These children will be only available for an intention-to-treat analysis. Thus, 100 children in each formula arm, as well as in the breastfed group will be included to have also sufficient power in a per-protocol analysis.

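### Section 9.11 sets out to confirm compliance with a between-arm t-test of intake, but that test addresses equality of arm means, not adherence to 5.4.1

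*Protocol*

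**What the plan says.** Section 9.11 gives the analysis both a purpose and a method. The purpose is in its opening words: "To confirm compliance with the study protocol energy intake and macronutrient intake as calculated from 3-day food protocols". The method is that these quantities "will be compared by t-test between both intervention groups", the groups being the two randomised formula arms. The section gives no adherence target, equivalence bound, significance level or rule for reading the result.

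Elsewhere the protocol treats compliance as a property of the individual infant:

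- Section 5.4 requires full feeding of the assigned formula from day 28 at the latest until day 120. Section 5.4.1 defines what counts as full feeding, with small tolerances.
- Sections 7.3.4, 8.5.2.2 and 8.7 check this at every visit and reminder call.
- Section 5.5.1 makes feeding outside the definition severe non-compliance. Sections 5.5.2 and 9.9 remove such infants from the per-protocol population, which is the primary analysis set.

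The two formulas differ in protein content, 1.89 against 2.2 g/100 kcal (6.1.1), and are fed ad libitum (6.2.1). Section 9.5 anticipates some departure from assigned feeding: "Additionally, we expect that another 15% will switch formula due to preference changes".

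**The concern.** The question asked is whether infants were fed as the protocol requires. The question tested is whether mean intake is the same in the two arms. One can hold without the other, so neither outcome of the test answers the question.

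Shared non-compliance is plausible here, because the arms are blinded (6.1.5) and the expected switching is attributed to preference changes, not to either formula. In a non-inferiority trial a reader will want to know how well each arm adhered, since departures common to both arms tend to make the arms look alike. A report stating that compliance was confirmed by this test would claim something the test cannot deliver.

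**Working it through.** **Inputs from the protocol.** Protein 1.89 and 2.2 g/100 kcal (6.1.1); about 70 completers and 100 recruited per arm (4.2, 9.5); weight-gain SD 6 g/d (9.5), margin 3 g/d (9.2), one-sided 2.5% and 85% power (9.5).

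**Assumptions, because the protocol gives no figure.** Two-sided 5% for the 9.11 tests; a coefficient of variation (CV) of intake of 15–25%, with 30% as a further case; 2.2 g/100 kcal for the protein content of any substitute feed.

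**The plan's own figure.** Section 9.11 contains no number. The sample size in 9.5 reproduces: n = 2 × (1.960 + 1.036)² × 6²/3² = 71.8, so 72 per arm, against the stated "Thus, one would need about 70 children in each formula group"; and 70/0.70 = 100. This does not bear on the present point.

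**Step 1, energy.** Let μ be mean energy from study formula under full compliance, and let both arms fall short by a fraction f. The difference the t-test addresses is (1 − f)μ − (1 − f)μ = 0 for every f. The null stays true, and the chance of a non-significant result is 1 − α: 95% at two-sided 5%, 97.5% at one-sided 2.5%. Simulation (20,000 replicates; 70 or 100 per arm; CV 15–25%) returned 94.7–95.3% at f = 0, 0.25 and 0.50. That is the arithmetic of a true null; what matters is that it does not move with f. If diary energy counts all feeds and not only study formula, an infant switched to another formula may show no shortfall at all, and the test is equally uninformative.

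**Step 2, non-significance is not equality.** With 70 per arm, the 95% CI half-width for the mean difference, as a share of mean intake, is 1.96 × CV × √(2/70) = 0.331 × CV.

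| CV (assumed) | Half-width | Far end of the CI when the result just misses significance |
|---|---|---|
| 15% | 5.0% | 10% |
| 20% | 6.6% | 13% |
| 25% | 8.3% | 17% |

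**Step 3, several nutrients.** The 95% is for one test. With four tests (energy, protein, fat, carbohydrate) and equal means throughout, all four are non-significant with probability 0.95⁴ = 81.5% if independent, and 84.5%, 90.7% and 93.7% at correlations of 0.5, 0.9 and 0.99. No single figure describes the whole of 9.11, and equal means is not the expected state for protein.

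**Step 4, protein.** At equal energy intake, full compliance gives a difference of 2.2 − 1.89 = 0.31 g/100 kcal, or 0.31/2.2 = 14.1%. With 70 per arm and CV 25%:

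- SE = √[((0.25 × 1.89)² + (0.25 × 2.2)²)/70] = 0.0867
- 0.31/0.0867 = 3.58
- the chance of non-significance is about Φ(1.96 − 3.58) = 5%

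The simulation gave 5.6% here and 0–5.6% over CV 15–25% and 70 or 100 per arm. At CV 30% and 70 per arm, about 16% are non-significant (84% reject). So with everyone compliant, a significant protein result is what should be seen.

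If a fraction f of energy in both arms comes from the substitute feed, the difference shrinks to (1 − f) × 0.31: 0.2325 (10.6%) at f = 0.25 and 0.155 (7.0%) at f = 0.50. Non-significance then rises to 0.1–25% and 7.5–60%. The protein comparison therefore has some sensitivity to shared switching, but in the opposite direction to the energy comparison.

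**Step 5, a significant energy result.** Feeding is ad libitum, so fully compliant arms may take different amounts. A significant energy difference would not show non-compliance either.

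**The case against.** The strongest reply is that 9.11 is only loosely worded. Section 2 describes an earlier protein trial in which energy intake was similar between formula arms and protein intake was higher in the high-protein arm. Read in that light, 9.11 is an intake-contrast check and a protein difference is the result hoped for. That is a sensible analysis, and it should be kept under that description. It still compares arms and says nothing about how many infants met 5.4.1, so the stated purpose remains unmet. Detail on reporting could sit in an SAP, but the protocol itself pairs this purpose with this test.

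Three stronger readings are tempting, and the documents do not support them:

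- *That the trial will declare compliance about 95% of the time regardless.* Section 9.11 contains no rule turning a non-significant result into a finding of compliance, and states no level. The 95% is 1 − α for one test at an assumed level.
- *That this test is the trial's safeguard against shared non-compliance, so the non-inferiority conclusion is exposed.* It decides no analysis set. Infant-level checks at visits and calls, formula accounting (6.2.3, 6.4.2) and the Visit 4 record (8.5.3.1) serve that role, and 9.5 leaves switchers to the intention-to-treat analysis only.
- *That non-study feeds go unquantified in the formula arms.* Section 6.3.1 asks for the kind, frequency and amount of concomitant diet, and 8.6 has it written in the diaries. How diary entries become energy and macronutrients is not described, and the diary form is not shown.

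**Conclusion.** Wrong as written, minor. The comparison in 9.11 cannot confirm compliance. For energy, a single test is non-significant with probability 1 − α under any degree of non-compliance shared equally by both arms. For protein, full compliance makes the null false by about 14% at equal energy intake, so one sentence applies one test to nutrients whose results need opposite readings and gives a rule for neither.

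The mismatch between purpose and null hypothesis needs no assumption. The simulated percentages depend on the assumed 5% level, intake CVs and substitute feed, and serve only as illustration. What is affected is what the trial may say about compliance. Per-protocol membership and the primary weight-gain comparison are not directly affected.

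**What to change.** Reword 9.11 and add one table.

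1. Describe the analysis as a between-arm comparison of diary energy and macronutrient intake, reported as mean difference with 95% CI.
2. State that a protein difference is expected by design and that the comparison is not evidence of compliance.
3. Report compliance as the proportion of infants in each formula arm meeting 5.4.1, with 95% CI, from the visit and reminder-call records.

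The cost is a few sentences and one table. The visit and call data are already collected, so no new measurement is needed. Setting diary volumes against the formula accountability records is not recommended as part of this change: diaries cover three days before each visit (8.6), while boxes are dispensed to cover weeks and unused ones come back only at Visit 4 (6.2.3, 6.4.1), so the two do not match without extrapolation.
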